### Strategies to improve adherence to interventions {11c}

All patients will fill out a daily diary and evaluate each therapy session. Adherence will be assessed by reviewing these documents. The team of the process evaluation will be responsible for the evaluation of the diaries. Likewise, close contact with the multiplier, regular visits, and therapies as individual therapy and in small groups should contribute to patients’ motivation and adherence to therapy.

### Relevant concomitant care permitted or prohibited during the trial {11d}

Participation in other intervention studies is prohibited (see exclusion criteria). However, it is allowed to treat the laboratory parameters collected in the recruiting clinic in case of abnormalities during prehabilitation. Likewise, medications can be adjusted for discomfort and/or cardiac and/or non-cardiac abnormalities.

### Provisions for post-trial care {30}

The study ends for all participants after the assessment t6 (follow-up 1 year after the cardiac procedure). All patients will sign the patient consent at the beginning of the study which includes the information that they agree to voluntarily participate in the clinical trial. The patient consent/information is available on request by the corresponding author. Participants carry no additional costs for post-trial care due to the fact that the German healthcare system does not require those who are insured to pay deductibles, co-payments, or out-of-pocket fees to receive medical care.

### Outcomes {12}

The co-primary outcomes are the QoL and mortality after 12 months. The QoL is measured by the EuroQol questionnaire (EQ-5D-5L, [23]). The EQ-5D-5L consists of five dimensions (mobility, self-care, usual activities, pain/discomfort, and anxiety/depression) and is an instrument for measuring QoL and determining quality-adjusted life years in health economic studies [23, 24]. Each dimension is scored on a 5-point scale. The responses to the individual items are combined into a QoL index using established algorithms. In addition, patients rate their health status on a visual analog scale (EQ-VAS; range 0–100) [23].

The following secondary outcomes measures are defined:Activities of daily living (ADL) measured by Katz Index [25, 26]Physical performance rated by Short Physical Performance Battery (SPPB; [27])Cognitive performance measured by Montreal Cognitive Assessment Test (MoCa; [28, 29])Disease-specific QoL assessed by Heart Quality of Life Questionnaire (HeartQoL; [30])Anxiety and depression detected by Hospital Anxiety and Depression Scale (HADS; [31–33])Healthcare costs after 12 months. Healthcare resource utilization within 12 months after the cardiac procedure. During follow-up, all direct medical and non-medical healthcare-related resource utilization will be monitored using a validated questionnaire for health-related resource use by older patients (Fragebogen zur Inanspruchnahme medizinischer und nicht-medizinischer Versorgungsleistungen im Alter (FIMA; [34]) in combination with routine data transmitted by the AOK Lower Saxony and AOK Baden-Württemberg.

Further endpoints are as follows:

Thirty-day mortality, length of stay in intensive and normal care unit, AE/SAE assessment, hand strength measured by Marin-Vigorimeter [35, 36], functional capacity collected by the 6-min walk test [37], bioelectrical impedance analysis to elevate body composition [38], Mini Nutritional Assessment to detect malnutrition [39, 40], Pittsburgh Sleep Quality Index to detect sleep quality [41–43], Maastricht Questionnaire to evaluate the vital exhaustion [44, 45], Informant Questionnaire on Cognitive Decline in the Elderly to assess opinion of relatives (IQCODE; [46]; Zarit Burden Interview to measure burden of relatives (G-ZBI; [47]), Clinical Frailty Scale to assess frailty (CFS; [48]), American Thoracic Society (ATS) scale to evaluate dyspnea (dyspnea scale of the ATS; [49]), self-reported subjective memory impairment (SMI; [50]) to measure patients’ opinion about the own memory performance, Selbstwirksamkeits-überzeugung ([general self-efficacy scale], SWE) scale to identify self-efficacy expectancy [51–53], Hamburger Fragebogen zum Krankenhausaufhalt [Hamburg Questionnaire on Hospital Stay] to assess patients’ satisfaction with the hospital stay [54], optimism measured by Life-Orientation-Test revised (LOT-R; [55]), loneliness detected by UCLA Loneliness Scale [56, 57], illness perception measured by Illness Perception Questionnaire (IPQ; [58]), treatment expectancy measured by Treatment Expectation Questionnaire (TEX-Q; [59]), and institutionalization/dependence on care assessed in Clinical data / sociodemographic interview.

The mixed-methods process evaluation will evaluate intermediate outcomes (dose, reach, fidelity, adaptions) of the intervention [60]. It assesses the implementation of the prehabilitation itself and the reactions and perspectives of involved persons. Moreover, barriers and facilitating factors will be explored [61]. More details will be published in a separate study protocol.

### Participant timeline {13}

Table 4 summarizes the schedule of enrolment, intervention, and assessments in the PRECOVERY trial.

**Table 4 Tab4:** Schedule of enrolment, intervention, and assessments in the PRECOVERY trial

Time point	t0 (Screening)	t1 (Randomization/ Baseline)	t2 (Before CP)	t3 (After CP)	t4 (30 days after CP)	t5 (6 months after CP)	T6 (12 months after CP)
Inclusion/Exclusion criteria	x						
Informed consent, enrollment, allocation	x						
Medical history, social demographics		x					
**Primary Outcomes**							
EQ-5D-5L (QoL)		x	x	x	x	x	x
1-year mortality							x
**Secondary Outcomes**							
Katz Index (daily activity)		x	x	x	x	x	x
SPPB (physical performance)		x	x				x
MoCa (mental performance)		x	x				x
HeartQoL (disease-specific QoL)		x	x		x	x	x
HADS (anxiety and depression)		x	x		x	x	x
**Other Outcomes**							
30-day mortality					x		
Hand grip strength (frailty)		x	x				x
6-min walk test (functional capacity)		x	x				x
BIA (body composition)		x	x				x
MNA (frailty, malnutrition)		x	x				x
PSQI (sleep quality)		x	x				x
Maastricht questionnaire (vital exhaustion)		x	x		x		x
UCLA Loneliness Scale (loneliness)		x			x		x
SMI (memory impairment)		x	x		x	x	x
CFS (frailty)		x	x	x			x
Pre- and post-procedure complications				x			
Length of stay in intensive and normal care				x			
Institutionalization/dependence on care		x	x	x	x	x	x
ATS scale (dyspnea)		x	x	x	x	x	x
SWE scale (general self-efficacy)		x			x	x	x
HFK (patients ‘ satisfaction with hospital stay)				x			
LOT-R (optimism)		x	x				
IPQ-B (illness perception)		x	x				x
TEX-Q (treatment expectancy)		x	x				
Process evaluation		x	x	x	x	x	x
FIMA Questionnaire (healthcare-related resource utilization)		x				x	x
Blood sample		x	x	x			x
AE/SAE			x	x	x	x	x
**Relatives:** G-ZBI (burden of relatives)		x				x	x
**Relatives:** IQCODE (opinion of relatives)		x				x	x

Abbreviations: *AE* adverse event, *ATS* American Thoracic Society, *BIA* Bioelectrical Impedance Analysis, *CP* cardiac procedure, *CFS* Clinical Frailty Scale, *d* days, *EQ-5D-5L (QoL)* Euro Quality of Life, *FIMA* Fragebogens zur Erhebung von Gesundheitsleistungen im Alter [Questionnaire for the survey of health services in old age], *G-ZBI* German Zarit Burden Interview, *HADS* Hospital Anxiety and Depression Scale, *HeartQoL* Heart Quality of Life, *HFK* Hamburger Fragebogen zum Krankenhausaufhalt [Hamburg Questionnaire on Hospital Stay], *IPQ-B* Illness Perception Questionnaire, *IQCODE* Informant Questionnaire on Cognitive Decline in the Elderly, *LOT-R* Life Orientation Test Revised, *m* month, *MNA* Mini Nutritional Assessment, *MoCa* Montreal Cognitive Assessment Test, *PSQI* Pittsburgh Sleep Quality Index, *SAE* serious adverse event, *SMI* Self-reported subjective memory impairment, *SPPB* Short Physical Performance Battery, *SWE* Selbstwirksamkeits-überzeugung ([Self-efficacy beliefs], *TEX-Q* Treatment Expectation Questionnaire, *UCLA* University of California Los Angeles

### Sample size {14}

A total number of 422 patients is planned for this intervention trial. The number of cases was planned on a confirmatory basis in order to be able to answer the primary questions with a power of 80%. A total of 338 patients (169 per treatment group) is sufficient to show a clinically relevant difference of 0.045 points in EQ-5D-5L at t6 with 80% power at the generally accepted two-sided significance level of 5%. It is assumed that the common standard deviation of the EQ-5D-5L is 0.17 and that the observations on the covariates have an R-squared of 0.25. Since this is a longitudinal study, a dropout rate of up to 20% is assumed, so a total of 422 patients will be recruited. The case number calculation was performed in nQuery version 8. The definition of a clinically relevant difference of 0.045 was based on the publication of McClure et al. [62], who restricted a minimal clinically relevant difference to values between 0.037 and 0.069 [62]. Since the publication did not include results on the German population, a value was chosen that was approximately 10% lower than the average of the countries considered in the publication. The assumption of a standard deviation of 0.17 is based on observations by [63], who observed a standard deviation of 0.171 at baseline and a standard deviation of 0.170 at 12-month follow-up in a sample of 1927 diabetes-2 patients [63].

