### Trial design {8}

PRECOVERY is a confirmatory, randomized, controlled, two-arm parallel group, assessor-blinded multicenter intervention trial. If positive, we will confirm the efficacy of the multimodal prehabilitation intervention with regard to patients’ QoL, medical, cognitive, and psychosocial outcomes 12 months after an elective cardiac procedure. We will randomize 422 patients aged 75 years or older scheduled for an elective cardiac procedure to either (a) SMC (*n* = 211) or (b) a 2-week multimodal prehabilitation intervention (“Karl-Heinz”, *n* = 211) with an allocation ratio of 1:1 per hospital, patient’s age and gender with a follow-up period of 12 months. An additional component of the RCT is a detailed health economic analysis by the Department of Health Economics and Health Services Research, University Medical Center Hamburg-Eppendorf, Germany. Furthermore, an independent process evaluation in a mixed-methods design will be provided by the Department of General Practice of the University Medical Center Goettingen, Germany.

The primary aim is to demonstrate superiority of the intervention group compared to SMC group in terms of QoL and mortality 12 months after the cardiac procedure. The secondary aim is to show the superiority of the intervention group compared to the SMC group in terms of functional and cognitive capacity, heart-specific QoL, and activities of daily living after 12 months.

For the health economic analysis, we anticipate at least equivalence, a better non-inferiority in healthcare costs after 12 months in the intervention group compared to SMC group.

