### Eligibility criteria {10}

We will include patients 75 years or older undergoing elective cardiac procedures defined by the German operation and procedure codes catalog (OPS, see Table 1). Due to legal reasons to the project funding participation of patients included in Lower Saxony is limited to patients of AOK Lower Saxony public health insurance provider.

**Table 1 Tab1:** Explanation of the translated OPS Code

OPS Code and Procedure
5–35: Operations on heart valves and septa as well as on vessels close to the heart
5–351: Replacement of heart valves with prostheses
5–352: Change of heart valve prostheses
5–353: Valvuloplasty
5–354: Other operations on heart valves
5-35a: Minimally invasive surgery on heart valves
5–36: Coronary artery surgery
5–360: Desobliteration (endarterectomy) of coronary arteries
5–361: Creating an aortocoronary bypass
5–362: Creating an aortocoronary bypass using minimally invasive technique
5–363: Other revascularization of the heart

*Abbreviations OPS* operation and procedure codes

An adapted recruitment strategy has been developed as an option for the case that the number of eligible ≥ 75 years old AOK-insured persons is not adequate to reach our recruitment goals. First, the age requirement will be lowered by 10 years to include all retired persons ≥ 65 years. PRECOVERY is powered to EQ-5D-5L with a minimal clinically relevant effect. Current literature shows a positive effect of prehabilitation on QoL also in patients who are ≥ 53 years of age [18, 19]. The costs for prehabilitation are covered by the health insurance for retired persons; however, the pension fund is responsible for such costs for employed persons. Therefore, PRECOVERY is only open to retired persons. Second, by continued recruitment problems the study will be opened to include members of all health insurance companies.

Inclusion and exclusion criteria are summarized in Table 2.

**Table 2 Tab2:** PRECOVERY inclusion and exclusion criteria

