## Statistical methods

### Statistical methods for primary and secondary outcomes {20a}

Details on statistical analysis are described in a statistical analysis plan (see Additional file 2). The primary endpoint EQ-5D-5L will be evaluated using a joint model for longitudinal data. Stratification factors of age, sex, participation in DMPs, and center will be included as covariates in the model. Time courses of EQ-5D-5L are presented longitudinally for each group, and survival rates are presented descriptively using Kaplan–Meier curves. Treatment effects are reported with 95% confidence intervals. The secondary endpoint HeartQoL is evaluated analogously to the primary endpoint. Secondary endpoints Katz Index, SPPB, MoCa, and HADS are evaluated using mixed linear models, with the factors time point, treatment, and the interaction, and the covariates age, sex, DMP participation, and center. Marginal means are calculated for inter- and intra-group comparisons, and treatment effects are reported with 95% confidence intervals. Likewise, for the analysis of the health economic outcomes, mean differences are calculated in mixed regression models. Because of the skewed distribution of the cost data, the non-parametric bootstrapping procedure, which is also used in the uncertainty analysis of the incremental cost-effectiveness ratio (ICER), is additionally used to calculate the standard errors of the regression parameters. For the analysis of cost-effectiveness, the net-benefit regression procedure is used. Details can be found in the Additional file 1 “Study Protocol”.

Statistical methods in the process evaluation:

For the process evaluation, exploratory sensitivity analyses will be performed to assess the impact of dose, reach, fidelity, and adaption on the intervention’s efficacy. For this purpose, interaction-terms between the treatment variables and these factors will be included in the mixed linear models described above. In addition to the intention-to-treat population, a population will be defined that started the intervention as intended and stays adherent during the follow-up period (starting and adhering estimand).

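### The 80% power claimed for the primary questions is calculated for EQ-5D-5L only; co-primary mortality has no stated power, and the article names no mortality test

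*Protocol article*

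**What the plan says.** The Outcomes section {12} states: "The co-primary outcomes are the QoL and mortality after 12 months". Trial design {8} calls the trial confirmatory and sets out to "demonstrate superiority of the intervention group compared to SMC group in terms of QoL and mortality 12 months after the cardiac procedure". Objectives {7} puts both endpoints into the primary research question.

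Sample size {14} says the number of cases was "planned on a confirmatory basis in order to be able to answer the primary questions with a power of 80"%, with the primary questions in the plural. The calculation that follows is for a "clinically relevant difference of 0.045 points in EQ-5D-5L at t6", "with 80% power at the generally accepted two-sided significance level of 5"%, with an SD of 0.17 and a covariate R-squared of 0.25. It gives 169 evaluable patients per arm, 338 in total, raised to 422 for up to 20% dropout. The section contains no mortality rate, mortality effect, event count or mortality power. Eligibility criteria {10} describes the scope more narrowly: "PRECOVERY is powered to EQ-5D-5L with a minimal clinically relevant effect".

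Statistical methods {20a} assigns EQ-5D-5L to a joint model for longitudinal data. It says that "survival rates are presented descriptively" with Kaplan–Meier curves and that treatment effects carry 95% confidence intervals. It names no test or effect measure for mortality, and does not say whether the joint model has a survival part. Details are referred to an SAP and a full protocol that are not at hand.

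**The concern.** A power statement tells the reader which hypotheses the trial can settle. This one covers two confirmatory hypotheses but is supported by a calculation for one. Within the same article, the aim is superiority on mortality, the sample size section offers nothing for mortality, and the methods section presents survival descriptively. These statements do not fit together as written.

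The consequences depend on the success rule:

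- If both endpoints must succeed, the power of the trial is capped by its mortality power, whatever the power for EQ-5D-5L.
- If the 5% is shared between the endpoints, the stated 80% no longer holds for EQ-5D-5L at the planned size.
- If mortality is only described, the stated primary aim cannot be met for that endpoint.

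Under any of these, a reader could take a neutral mortality result as coming from a test with 80% power.

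**Working it through.** **1. Reproduce the plan's figure (inputs from Sample size {14}).**
Residual SD = 0.17 × √(1 − 0.25) = 0.1472.
n per arm = 2 × [0.1472 × (1.960 + 0.842) / 0.045]², rounded up = 169.
Standard error at 169 per arm = 0.1472 × √(2/169) = 0.01602, and 0.045 / 0.01602 = 2.810.
Power = Φ(2.810 − 1.960) = Φ(0.850) = 80.2% (80.0% with the noncentral t).
338 / 0.8 = 422.5, in line with 422.
The stated size is therefore correct for EQ-5D-5L alone, and it uses the whole two-sided 5%.

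**2. Mortality power.**
The article gives no planning rate, so control risk and effect are assumptions. The number per arm is 211 (Trial design {8}), which assumes vital status is known for everyone and so favours the trial.
Power = Φ[(d − 1.960 × se0) / se1], where d is the risk difference, se0 the pooled and se1 the unpooled standard error.

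Example, 10% against 6.67%:
- d = 0.0333 and pooled risk = 0.0833
- se0 = √(0.0833 × 0.9167 × 2/211) = 0.02691
- se1 = √[(0.10 × 0.90 + 0.0667 × 0.9333)/211] = 0.02686
- power = Φ[(0.0333 − 0.0527)/0.02686] = Φ(−0.72) = 23.5%

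| Relative reduction (assumed) | Control 5% | Control 10% | Control 15% | Control 20% |
|---|---|---|---|---|
| One quarter | 9.1% | 14.6% | 20.6% | 27.1% |
| One third | 13.5% | 23.5% | 34.2% | 45.1% |
| One half | 27.1% | 49.6% | 68.5% | 82.3% |

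In this grid, 80% is reached only when 20% mortality is halved. At 10% control mortality, 80% power would need a fall to about 3.2%.

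**3. If both endpoints must succeed.**
The probability of winning both cannot exceed the smaller of the two powers. At 10% control mortality and a one-third reduction, that ceiling is 23.5%. Under independence the figure would be 0.80 × 0.235 = 19%.

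**4. If the 5% were split equally.**
The critical value for EQ-5D-5L becomes 2.241. Power at 169 per arm = Φ(2.810 − 2.241) = Φ(0.568) = 71.5%, and 204 evaluable per arm would be needed for 80%.

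**The case against.** Several points on the other side stand.

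- **Disclosure.** Eligibility criteria {10} says openly that the trial is powered to EQ-5D-5L, so a careful reader is not wholly misled. This confirms that the sample size sentence is too broad, but it does not correct it.
- **Decision rule.** A reader might infer that the trial has no rule on whether both endpoints or either must succeed. The article cannot show that. Such rules and the handling of alpha are commonly left to the SAP, which is not at hand.
- **Mortality analysis.** A reader might infer that mortality will only be described. The Kaplan–Meier clause concerns presentation. The article also uses a joint model for EQ-5D-5L and mixed linear models for other outcomes, which is compatible with a survival part in the joint model. What can be said is that the article names no mortality test.
- **Singular wording.** Calling EQ-5D-5L the primary endpoint in {20a} does not demote mortality. The same paragraph calls HeartQoL the secondary endpoint although it is one of several.
- **Size of the mortality power.** No single figure or narrow band is established, since the result depends wholly on the assumed rates. The one mortality figure in the Introduction, up to 40%, concerns frail or delirious patients and is not a planning rate for this trial.
- **Error inflation.** Two independent tests at 5% each would give 1 − 0.95² = 9.75% familywise error, but nothing in the article says that either endpoint alone suffices. If both are required, 5% for each is correct.

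None of this extends the calculation in {14} to mortality. An SAP could settle the success rule, but it could not make a calculation built on EQ-5D-5L inputs answer a mortality question.

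**Conclusion.** The concern holds in a limited form. The power statement in Sample size {14} is wrong as written: 80% is shown for EQ-5D-5L at t6 and for nothing else. The article also leaves its mortality superiority aim unreconciled with a methods section that names no mortality test and presents survival descriptively.

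The EQ-5D-5L part rests only on the plan's own inputs. The mortality part is conditional: about 9% to 82% over assumed control mortality of 5% to 20% and relative reductions of one quarter to one half, with 211 per arm and two-sided 5%. The documents do not support the stronger conclusions that mortality goes untested, that no success rule exists or that the type I error is inflated.

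**What to change.** 1. In Sample size {14}, state that the 80% applies to EQ-5D-5L at t6 at two-sided 5% and that the trial is not powered for mortality. Give the mortality power over a range of assumed control rates and effects, labelled as assumptions.
2. Reconcile Trial design {8} with Statistical methods {20a} by reporting a between-group mortality effect with a 95% confidence interval, from the survival part of the joint model if it has one or otherwise from a Cox model. Keep the Kaplan–Meier curves as a supplement.
3. Make the wording on whether both endpoints or either one is required agree with the SAP wherever the co-primary endpoints are described.

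Making EQ-5D-5L the sole primary endpoint, with mortality tested after it, is a further option but not a necessary one. It would change a hypothesis after enrolment began in April 2023 and would need an ethics amendment under section {25}.

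The cost is a change of text and one reported effect estimate, with no extra patients or data. The stated power becomes less favourable.

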### Recruitment {15}

The recruitment measures in PRECOVERY are integrated into the standard procedures of the participating recruiting centers. In these centers, patients scheduled for cardiac procedures in 4–6 weeks will be screened, informed, recruited (t0), and randomized (t1) according to the inclusion and exclusion criteria during a preoperative appointment in cardiology or cardiac surgery departments. To support the recruitment process, all referring centers will be informed about the study in advance and additional flyers will be produced to increase patient interest.

If the recruitment is not running well, the evaluation concept is designed through the use of the FIMA questionnaire in such a way that an extension to the inclusion of insured persons from other health insurance funds is also conceivable in Lower Saxony on the basis of the legal basis §630a German civil code.

